# Within-subject effects of standardized prosthetic socket modifications on physical function and patient-reported outcomes

**DOI:** 10.1186/s13063-022-06205-z

**Published:** 2022-04-12

**Keywords:** Limb prosthetics, Motion analysis, Dynamic radiography, Randomized controlled trial

## Abstract

**Background:**

Among the challenges of living with lower limb loss is the increased risk of long-term health problems that can be either attributed directly to the amputation surgery and/or prosthetic rehabilitation or indirectly to a disability-induced sedentary lifestyle. These problems are exacerbated by poorly fit prosthetic sockets. There is a knowledge gap regarding how the socket design affects in-socket mechanics and how in-socket mechanics affect patient-reported comfort and function. The objectives of this study are (1) to gain a better understanding of how in-socket mechanics of the residual limb in transfemoral amputees are related to patient-reported comfort and function, (2) to identify clinical tests that can streamline the socket design process, and (3) to evaluate the efficacy and cost of a novel, quantitatively informed socket optimization process.

**Methods:**

Users of transfemoral prostheses will be asked to walk on a treadmill wearing their current socket plus 8 different check sockets with designed changes in different structural measurements that are likely to induce changes in residual limb motion, skin strain, and pressure distribution within the socket. Dynamic biplane radiography and pressure sensors will be used to measure in-socket residual limb mechanics. Patient-reported outcomes will also be collected after wearing each socket. The effects of in-socket mechanics on both physical function and patient-reported outcomes (aim 1) will be assessed using a generalized linear model. Partial correlation analysis will be used to examine the association between research-grade measurements and readily available clinical measurements (aim 2). In order to compare the new quantitative design method to the standard of care, patient-reported outcomes and cost will be compared between the two methods, utilizing the Wilcoxon-Mann-Whitney non-parametric test (aim 3).

**Discussion:**

Knowledge on how prosthetic socket modifications affect residual bone and skin biomechanics itself can be applied to devise future socket designs, and the methodology can be used to investigate and improve such designs, past and present. Apart from saving time and costs, this may result in better prosthetic socket fit for a large patient population, thus increasing their mobility, participation, and overall health-related quality of life.

**Trial registration:**

ClinicalTrials.gov NCT05041998. Date of registration: Sept 13, 2021.

## Administrative information

Note: The numbers in curly brackets in this protocol refer to SPIRIT checklist item numbers. The order of the items has been modified to group similar items (see http://www.equator-network.org/reporting-guidelines/spirit-2013-statement-defining-standard-protocol-items-for-clinical-trials/).

## Introduction

### Background and rationale {6a}

#### Importance of the problem

People with lower limb loss are at risk for a variety of chronic health challenges including cardiovascular diseases, osteoarthritis, low-back pain, obesity, and depression [1, 2]. The nature of those comorbidities differs substantially between patients who underwent amputation surgery as a consequence of vascular disease, such as diabetes, and those who experienced a traumatic amputation.

Among the civilian population, vascular disease is the predominant cause of limb loss [3]. Patients are typically older [4] and have a long history of disease manifestations involving the limbs, which include claudication, neuropathy, and tissue necrosis. The debilitating effects of these can contribute to a reduced activity level, sedentary lifestyle, obesity, and associated poor overall health. Because amputation surgery does not cure the underlying systemic diseases in this population, it is generally a last resort to address life-threatening limb complications. Even so, life expectancy after the surgery is limited [5, 6], and rehabilitation goals realistically are modest. Frequently, patients will not regain walking ability and remain constrained to wheeled mobility aids [7]. Prosthetic technology, if it is considered, generally reflects the limited rehabilitation goals in that prescribed functional components emphasize safety over dynamic efficiency and that prosthetic sockets are designed to be comfortable and easy to use at the expense of rigid suspension and controllability.

Limb loss after trauma is less prevalent in the overall population but is disproportionally common in the military population. While rehabilitation after combat-related amputations comes with its own set of challenges [8], including severe accompanying conditions such as complicated fractures, volumetric muscle loss, and traumatic brain injuries, the basic physical health of the patient is generally much better than in the average dysvascular amputation candidate [9]. This, along with the comparably young age of patients, calls for much more ambitious rehabilitation goals, including the full reconstitution of physical performance, participation in social life and gainful employment, and return to active duty [10]. Prescribed prosthetic components, such as knees and foot/ankle units are designed to support dynamic activity. The prosthetic socket may likewise be designed to be more functional and less comfortable, for instance, by providing a rigid ischial containment to prevent relative motion between the residual limb and prosthesis.

While people with traumatic limb loss are less at risk for sequela of a disability-induced sedentary lifestyle, they are nonetheless hampered by acute and chronic prosthesis-related conditions such as residual limb skin problems, low back pain, and osteoarthritis in the contralateral limb due to altered and excessive tissue loading during gait [11–13]. These problems are exacerbated by the limitations inherent in trying to reconcile the different objectives of prosthetic socket fit. There exists a belief among prosthetists that limiting skin strain and residual femur motion within the socket can minimize primary and secondary pathologies related to prosthesis use, and therefore, a prosthetic socket will always require unphysiological tight skin contacts and localized pressures. It has been proposed to avoid sockets entirely and attach prosthetic limbs directly to the residual bone using osseointegrated implants. Despite the great advancements that have been achieved with this approach in recent years [14], osseointegration may not be indicated for many individuals, either due to bone composition and co-morbidities [15] or to its incompatibility with high-impact activities such as running and sprinting [16] that military amputees may experience in the field. The more viable approach instead is to improve socket prostheses for this patient population.

#### Critical needs

People with lower limb loss experience chronic health challenges such as residual limb skin problems, low back pain, and osteoarthritis due to altered and excessive tissue loading during gait [11–13]. These problems are exacerbated by poorly fit prosthetic sockets. The goal for prosthetists in optimizing socket design is to improve function with a minimum of added discomfort. However, achieving an optimal balance between function and discomfort is currently a long, iterative process that is further frustrated by the absence of quantitative data [17, 18]. Instead, subjective patient feedback and coarse outcome assessments guide the repeated modifications. The lack of objective data also limits one’s ability to predict long-term outcomes (e.g., prosthesis-related tissue degradation).

There is a knowledge gap regarding how the socket design affects in-socket mechanics and how in-socket mechanics affect patient-reported comfort and function (Fig. 1). Prosthetists believe that limiting residual femur and skin motion will improve socket function. However, there are no data to (1) indicate how socket design is related to these variables, (2) prescribe changes in a socket that will reduce these movements, and (3) confirm that reductions in residual femur and skin motion will improve patient-reported outcomes [19–22]. Consequently, there is a real need for an experimental approach to better understand the relationship between socket design and the dynamic response of the residual limb within the socket.

**Fig. 1 Fig1:**
[figure not shown]
Key socket design parameters, in-socket mechanical factors, and patient outcomes

Although there are many types of prosthetic sockets marketed for transfemoral amputees, all are typically designed from a cast of the residual limb, do not account for soft tissue deformation and focal regions of high loading that develop during dynamic activities such as walking, and eventually lead to problems such as pressure ulcers, chronic skin problems, excessive joint loading, and an overall decreased quality of life for the amputee [23, 24].

Basic socket design principles have evolved steadily throughout the history of prosthetics and continue to be the subject of innovation. In trans-femoral prosthetics alone, a fairly large variety of basic design concepts are being discussed and marketed today, including varieties of ischial containment sockets (CAT-CAM, MAS) [25, 26], sub-ischial brimless designs (NUFlex, MWK) [27], “bionic” interface (HiFi, PBSS) [28], and adaptable frame designs (Infinite, Socket-less socket) [29], all claiming to entail substantial benefits and being widely indicated across the patient population. There is no scientific data and very little reliable empirical data to guide a choice of lower limb prosthesis from the available options. Because of this, any useful experimental approach for evaluating socket design on a patient-specific basis must be compatible with a patient group that uses a variety of different types of prosthetic sockets.

The socket optimization process involves refining the socket to optimize fit and function on a patient-specific basis. Socket optimization is an iterative process and dependent upon the experience and preferences of the prosthetist. There are some generally agreed upon (and taught) principles in optimizing socket fit, including, for example, local or general modifications of the socket volume, which are based on the observed difficulty of donning, skin discolorations, and patient-reported pressure points. The commonly applied process entails an iterative adjustment and reassessment of socket fit until a mutually (by patient and prosthetist) agreeable solution has been reached. However, there are many different approaches to such volume modifications. If a patient complains about a local pressure point, one prosthetist may decide to widen the socket in the respective area to relieve that pressure. Another prosthetist may narrow the socket in the area around the problematic spot in an effort to properly redistribute the contact force. Yet another may reduce the volume in the distal zones of the socket and reduce the length in order to reduce vertical displacement that, along with the conical shape of the limb, may originally have caused the intolerable contact pressure. The individual course of action thus depends on the suitability of the used assessment methods, the prosthetist’s interpretation of the issue, and his or her preference and experience.

#### Prior research

We recently completed a study on 12 transfemoral amputees that demonstrates our abilities to complete the proposed study [30, 31]. In that study, we used dynamic biplane radiography to measure residual bone motion and skin deformation within the socket during gait for three steps in each of the12 transfemoral amputees. Dynamic biplanar radiography is an ideally suited technology for these purposes because it provides extremely accurate data (submillimeter accuracy) that can be collected at a high frequency (up to 150 images per second) to image motion within the socket during dynamic functional activities such as gait. Prior to testing, small (1–2 mm diameter) metal beads were secured to the skin of the residual limb prior to donning the socket (Fig. 2A). The participants then walked on a treadmill while biplane radiographs of the residual limb were collected at 100 images per second (Fig. 2B). The beads were identified in each pair of synchronized radiographs (Fig. 2C).

**Fig. 2 Fig2:**
[figure not shown]
Method for measuring skin strain. **A** Metal beads were placed in a grid pattern on the skin of the residual femur. **B** Synchronized biplane radiographs were collected during treadmill walking. **C** Each bead was identified on every pair of synchronized radiographs to measure skin deformation during gait

We measured the relative motion between beads as the skin deformed within the socket for each participant. Skin deformation (strain) was then calculated from late swing through the push-off phase of gait (Fig. 3).

**Fig. 3 Fig3:**
[figure not shown]
Skin strain within the socket during three instants of the gait cycle: late swing, foot strike, and midstance. The skin surface is color-coded according to skin deformation (strain). Note the region of high strain in the anterior-distal portion of the residual limb

The feasibility of measuring in-socket pressure during gait was also successfully demonstrated on one subject (Fig. 4).

**Fig. 4 Fig4:**
[figure not shown]
In-socket pressure measurement. **A** Pressure sensors were attached to the skin prior to donning the socket. **B** In-socket pressure was measured during gait. Each colored line represents the total pressure recorded by one of four sensor pads during 5 s of gait

After lab testing, a CT scan of the residual femur was collected. The bone tissue was segmented from the CT scan and used to create a patient-specific 3D model of the residual femur. We then used our validated model-based tracking system to measure the motion of the residual femur within the socket by matching the femur bone model to the synchronized biplane radiographs (Fig. 5).

**Fig. 5 Fig5:**
[figure not shown]
Residual femur position within the socket of a transfemoral amputee at late swing during the gait cycle

That study demonstrated feasibility for this proposed study, allowed us to refine our data collection and analysis methods, and provided novel data to characterize the dynamic in-socket mechanics of transfemoral amputees. Over the course of that study, we developed a method to secure markers onto the skin in a grid pattern with a sufficient number of markers to obtain smooth, continuous skin deformation measurements. Importantly, none of the patients reported discomfort during gait due to the small markers secured to their skin. We were also able to identify an imaging configuration for the biplane radiography system that allowed us to image the residual limb from late swing through push-off with limited or no occlusion from the contralateral leg in the biplane radiographs. One encouraging finding was the repeatability of the in-socket mechanics. Although each participant demonstrated unique skin and residual femur movement patterns, within participants these in-socket mechanics were repeatable from trial to trial. One unexpected finding was the magnitude and rate of skin strain during the late swing phase. We had anticipated the greatest skin strain would occur after foot strike; however, our findings suggest that the skin is stretched most rapidly during the late swing phase as the leg is extended just prior to foot strike and the prosthesis pulls on the residual limb. This period of high strain rate is then followed by less rapid skin deformation during the loading phase. Those findings highlight the value of measuring dynamic in-socket mechanics and have helped guide our experimental design for this proposed study.

### Objectives {7}

The objectives of this proposal are (1) to gain a better understanding of how in-socket mechanics of the residual limb in transfemoral amputees are related to patient-reported comfort and function, (2) to identify clinical tests that can streamline the socket design process, and (3) to evaluate the efficacy and cost of a novel, quantitatively informed socket optimization process.

Our scientific premise is that understanding the biomechanical interactions between the prosthetic socket and the residual limb is fundamental to improving socket design. In order to optimize socket fit and distribute dynamic loads, it is critical to understand how the residual limb tissues respond to the external loads during gait. We are proposing that the current socket optimization process, which focuses exclusively on the relationship between socket features and outcomes, can be improved and expedited by using a quantitatively informed iterative optimization process that can improve comfort and function and reduce long-term health effects along with the associated healthcare costs.

### Specific aims

This project is structured with three specific aims. Aim 1 will build a foundation by using research-grade tools and technology to identify the relationship between socket design, in-socket mechanics, and patient-reported comfort and function. Aim 2 will identify readily available clinical measurements that are associated with in-socket mechanics during dynamic activities. Findings from aims 1 and 2 will be used to develop a quantitatively informed design optimization process that will be evaluated and compared to the current standard of care in a pilot clinical trial as part of aim 3. The specific aims and associated hypotheses are as follows.

#### Specific aim 1: Determine the relationship between in-socket mechanics and patient-reported comfort and function

The purpose of this aim is to reveal how in-socket mechanics, that is, (1) residual femur motion relative to the socket, (2) skin strain, and (3) pressure distribution, are related to socket design and patient-reported comfort and function. We hypothesize that (H1) the amount of residual bone motion, (H2) the peak rate of skin strain, and (H3) the peak pressure within the socket are associated with patient-reported comfort and function.

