#### Sample size {14}

To facilitate aims 1 and 2, GLM will be utilized, which is a flexible generalization of ordinary linear regression that allows for response variables that have error distribution models other than a normal distribution and is often robust to smaller sample sizes. With a sample size of *n* = 30 at 80% power and *α* = .05, we should be able to detect a moderate-to-large overall model effect (*f*^2^ = 0.45), while including all three in-socket mechanics. We will examine the effect(s) of each in-socket mechanical parameter on outcomes by utilizing the type III sum of squares tables. If our sample size drops below 30, we will develop separate models for each of the parameters of interest and outcome.

For aim 3, in order to compare the two methods of socket design (the quantitative design method compared to standard of care), we will compare patient-reported outcomes and cost between the two methods, utilizing the Wilcoxon-Mann-Whitney non-parametric test. With a sample size of *n* = 15 at 80% power and *α* = .05, we will be adequately powered to detect a moderate-to-large effect (*d* = 0.476) with respect to the differences in patient-reported outcomes and cost by method.

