##### Residual femur motion

Our validated volumetric model-based tracking system will match subject-specific 3D bone models to the biplane radiographs [42, 46] (Fig. 9). This tracking system has been validated in vivo to have an accuracy of 0.7 mm or better in translation and 0.9° or better in rotation [42] for 6 degree of freedom kinematics. Details describing the volumetric model-based tracking process, including hardware and software specifications, calibration and distortion correction procedures, and computational algorithms, have been described in detail [42, 47, 48]. The tracking process will yield the 3D motion of the residual femur during each walking trial. The dynamic 3D femur motion data will be smoothed using a fourth-order, low-pass Butterworth filter, with the filter frequency determined using residual analysis [49]. We will measure six degree of freedom motion of the femur relative to the socket (anterior-posterior, medial-lateral, and proximal-distal translation; anterior-posterior tilt, varus/valgus rotation, and internal/external rotation) and express our results as a percentage of the gait cycle. The analysis for aims 1 and 2 will focus on the medial-lateral and superior-inferior translation of the distal femur relative to the socket from late swing through midstance.

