##### Skin strain

The motion of the beads attached to the skin will be tracked using a custom software to identify the center of each bead in each pair of synchronized radiographs. This software finds bead centroids with an accuracy of 0.08 to 0.12 mm during dynamic movements [42, 43]. Skin strain will be calculated using freely available software (FEBio), with the zero strain value determined while wearing the socket but not bearing weight. Variability in the zero strain measurement will be determined by doffing and donning the socket three times and imaging the residual limb after each donning. The residual femur will be divided into 4 primary regions (anterior, medial, posterior, and lateral), with proximal and distal sub-regions within each region, resulting in 8 total regions. The average and peak skin strain within each region will be determined and expressed as a percentage of the gait cycle. The average values over all steps will be included as variables in the analysis for aims 1 and 2.

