##### In-socket pressure

We will measure peak pressure and area under the pressure versus the time curve recorded by each in-socket pressure sensor. Pressure will be measured for up to 6 steps per walking trial (i.e., 18 steps per socket) and the pressure results expressed as a percentage of the gait cycle (Fig. 4B). The average values over all steps will be included as variables in the aim 1 and aim 2 analysis.

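### Aim 1 H2 concerns the peak rate of skin strain but the stated analysis uses average and peak strain, and the aim 1 power fits about three predictors while more variables are sent to the analysis with no rule for choosing among them

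*Protocol article*

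**What the plan says.** **Hypotheses (Specific aim 1).** H1 is about the amount of residual bone motion. The other two are stated as "H2) the peak rate of skin strain, and (H3) the peak pressure within the socket are associated with patient-reported comfort and function".

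**Strain processing (Skin strain).** "The average and peak skin strain within each region will be determined and expressed as a percentage of the gait cycle". There are 8 regions. The section closes: "The average values over all steps will be included as variables in the analysis for aims 1 and 2". No rate is derived.

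**Pressure processing (In-socket pressure).** The measures are "peak pressure and area under the pressure versus the time curve recorded by each in-socket pressure sensor", and their step averages also go to the aim 1 and aim 2 analyses. The data-collection section gives four pads.

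**Femur processing (Residual femur motion).** "The analysis for aims 1 and 2 will focus on the medial-lateral and superior-inferior translation of the distal femur", that is, two translations.

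**Model (Statistical methods {20a}, Aim 1).** A generalized linear model with type III tests. The mechanics named as examples are bone motion, peak skin strain and pressure distribution. Separate models are planned only if fewer than 30 participants are available. Significant parameters are carried into a unified predictive model.

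**Power (Sample size {14}).** "With a sample size of *n* = 30 at 80% power" and α = 0.05, the detectable overall model effect is f² = 0.45, "while including all three in-socket mechanics".

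**The concern.** Two parts of the plan do not meet.

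First, the quantity in H2 is not the quantity analysed. Strain and strain rate are not interchangeable here. The Prior research section reports both magnitude and rate as unexpected. It places the fastest stretching in late swing, with slower deformation during loading, and says these findings helped guide the design. The article also keeps the terms apart elsewhere: aim 2 H3 concerns peak skin strain, while aim 1 H2 concerns its peak rate. An analyst who follows the processing and statistics sections would report on peak strain and leave H2 untested.

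Second, the power statement is for a model with three mechanics, but each mechanic arrives as several variables. If more than one per mechanic enters, the stated power no longer describes the model. If one per mechanic is picked after the data are seen, the selection is uncontrolled and feeds the unified model that aim 3 then uses. For scale, 26 candidates each tested validly at 0.05 would give 26 × 0.05 = 1.3 expected false positives per outcome if nothing were associated.

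**Working it through.** **1. Strain versus strain rate, side by side**

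- Specific aim 1, H2: peak *rate* of skin strain.
- Skin strain (processing): average and peak strain by region.
- Statistical methods, Aim 1: peak skin strain.
- Interim analyses {21b}: peak skin strain.

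No section derives a strain rate for this study. Strain rate otherwise appears only as a result of the earlier study. The raw material for it exists: beads are imaged at 100 images per second.

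**2. Variables sent to the aim 1 and 2 analyses**

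- Femur: 2 translations.
- Strain: 8 regions × 2 measures (average, peak) = 16.
- Pressure: 4 pads × 2 measures (peak, area under the curve) = 8.
- Total: 2 + 16 + 8 = 26, of which 24 are regional or by pad.

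Even with only one measure per region and per pad, the count is 2 + 8 + 4 = 14.

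**3. Reproducing the stated power**

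Inputs from Sample size {14}: N = 30, α = 0.05, power 80%, f² = 0.45, so R² = 0.45/1.45 = 0.31. The method is the overall F test of a multiple regression with u predictors: df1 = u, df2 = N − u − 1, noncentrality λ = f² × N. A more conservative convention takes λ = f² × df2.

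For u = 3: df2 = 26 and λ = 0.45 × 30 = 13.5.

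- Power is 82.7% (conservative convention, λ = 11.7: 76.4%).
- Smallest f² detectable at 80% power is 0.423 (conservative: 0.488), which brackets the stated 0.45.
- N needed for 80% power at f² = 0.45 is 29 (conservative: 32), against the stated 30.

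With two predictors the detectable f² is 0.36 to 0.40, and with four it is 0.48 to 0.58. Neither range contains 0.45. The stated figure is therefore a three-predictor figure.

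**4. Power at N = 30 and f² = 0.45 with more predictors**

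| Predictors u | df2 | Power, λ = f²N | Power, λ = f²·df2 | Detectable f² at 80% (λ = f²N) |
|---|---|---|---|---|
| 3 | 26 | 82.7% | 76.4% | 0.423 |
| 4 | 25 | 77.0% | 68.2% | 0.480 |
| 10 | 19 | 48.5% | 30.5% | 0.830 |
| 26 | 3 | 8.8% | 5.4% | 10.8 |

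Four predictors arise from the two femur translations plus one strain and one pressure variable. Ten is an illustration: two translations, one strain value for each of the four primary regions, and one pressure value for each of the four pads (2 + 4 + 4). The last row is the worst case in which all 26 enter one model.

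**The case against.** - **The article does not describe a 26-variable model.** This stands. A reader might infer from the processing sections that all 26 enter one regression, with about 9% power and 3 residual degrees of freedom. The text does not support that. It says the values enter the analyses for aims 1 and 2 together, aim 2 uses partial correlations where regional values have a natural use, the femur section says only where the analysis will focus, and the aim 1 list of mechanics is given as examples.

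- **One row per participant understates the data.** This also stands. Outcomes are averaged per intervention, and each participant walks in 9 sockets, giving up to 30 × 9 = 270 participant-socket rows. With 270 rows, 26 predictors leave 270 − 26 − 1 = 243 nominal residual degrees of freedom, and the R² expected from pure noise is 26/269 = 0.10, not the 26/29 = 0.90 that 30 rows would give. Saturation does not follow for the data to be collected. Nor is 270 the right number for power, because rows within a participant are correlated. The calculation above uses 30 because the protocol's own power statement does.

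- **H2 could still be answered.** True: rate is a derivative of a strain series already measured, and a condensed article may omit derivation steps. But the article does more than omit the rate. It names a different strain quantity in the processing, the model and the interim summaries.

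- **The trial is labelled exploratory, and the model is to be tested on 15 new participants.** This softens the selection concern. It does not reconcile H2 with its analysis or the power statement with the variables listed.

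The power statement itself does not mention strain rate. The rate comes only from the hypothesis.

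**Conclusion.** Two inconsistencies stand. The aim 1 analysis as written does not test H2, because the hypothesis is on the peak rate of strain and the analysis is on average and peak strain. This rests on the text alone and needs no calculation.

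The stated power (f² = 0.45 at n = 30) describes a model with about three predictors, while 26 variables are sent to the aim 1 and 2 analyses and nothing maps them to the three mechanics. On the protocol's n = 30 basis, one predictor beyond three already takes power from 83% to 77%, and ten takes it to 49%. These figures assume an overall F test, one row per participant and λ = f² × N; the conservative convention gives lower values throughout.

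The defensible conclusion is that the stated power does not describe the variables listed. True power is not known to be 9%, and the type III tests cannot be called meaningless, because no section puts all 26 variables in one model and the repeated sockets are outside the calculation. The point should be settled before analysis, since the chosen parameters feed aim 3.

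**What to change.** - **Name one variable per hypothesis for the aim 1 model:** a single bone-motion summary for H1, peak strain rate derived from the existing bead images for H2, and peak in-socket pressure for H3. State for each how regions, pads and directions are combined into that one value.
- **If peak strain is what is meant, reword H2** to say so. Either way, the hypothesis, the Skin strain section and the aim 1 statistical methods should name the same quantity.
- **Label the remaining values exploratory:** the other regional strain values, the other pad values and the area under the pressure curve.
- **Restate the power** for that three-variable model, taking account of the repeated sockets within each participant.

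Cost: one extra derived variable from images already planned, a recalculated power statement, and wording. No new measurement is needed. The downside is that regional detail becomes exploratory in aim 1.
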